## Abstract

**Background:**

The World Health Organization has formally recognized that healthcare professionals are at risk of developing mental health problems; finding ways to reduce their stress is mandatory to improve both their quality of life and, indirectly, their job performance. In recent years, particularly since the COVID-19 pandemic outbreak, there has been a proliferation of online interventions with promising results. The purpose of the present study is twofold: to test the effectiveness of an online, self-guided intervention, MINDxYOU, to reduce the stress levels of healthcare workers; and to conduct an implementation study of this intervention. Additionally, an economic evaluation of the intervention will be conducted.

**Methods:**

The current study has a hybrid effectiveness-implementation type 2 design. A stepped wedge cluster randomized trial design will be used, with a cohort of 180 healthcare workers recruited in two Spanish provinces (Malaga and Zaragoza). The recruitment stage will commence in October 2022. Frontline health workers who provide direct care to people in a hospital, primary care center, or nursing home setting in both regions will participate. The effectiveness of the intervention will be studied, with perceived stress as the main outcome (Perceived Stress Scale), while other psychopathological symptoms and process variables (e.g., mindfulness, compassion, resilience, and psychological flexibility) will be also assessed as secondary outcomes. The implementation study will include analysis of feasibility, acceptability, adoption, appropriateness, fidelity, penetration, and sustainability. The incremental costs and benefits, in terms of quality-adjusted life years, will be examined by means of cost-utility and cost-effectiveness analyses.

**Discussion:**

MINDxYOU is designed to reduce healthcare workers’ stress levels through the practice of mindfulness, acceptance, and compassion, with a special focus on how to apply these skills to healthy habits and considering the particular stressors that these professionals face on a daily basis. The present study will show how implementation studies are useful for establishing the framework in which to address barriers to and promote facilitators for acceptability, appropriateness, adoption, feasibility, fidelity, penetration, and sustainability of online interventions. The ultimate goal is to reduce the research-to-practice gap.

**Trial registration:**

This study was registered in ClinicalTrials.gov on 29/06/2022; registration number: NCT05436717.

## Background

Although stress levels among healthcare workers are normally high, they have been accentuated by the COVID-19 pandemic. Over the last two years, healthcare workers have had to deal with the same pandemic-related stressors as any other citizens, in addition to their specific job-related stressors: continued exposure to infection, longer shifts––which has led to inevitable physical exhaustion and neglect of important aspects related to a healthy lifestyle––and difficult decisions regarding how to prioritize available resources in order to treat their patients, among others [1, 2]. Subjection to this sustained pressure, which is added to the normally high care burden of healthcare workers, entails a risk factor for developing mental health problems, including anxiety disorders, depression, somatoform disorders, post-traumatic stress disorders, and even suicidal ideation [3, 4].

The World Health Organization (WHO) has formally recognized that healthcare professionals are at risk of developing psychopathological symptoms, particularly those working in public health, primary care, emergency departments, and intensive care units [5, 6], including personnel employed by nursing homes [7]. It is essential to take care of the mental health of healthcare workers, not only to improve their quality of life, but also because the success of their work largely depends on it. Hence, it is especially necessary in the current circumstances to offer these workers effective and highly adaptive strategies that will enable them to cope with the numerous stressors to which they are exposed in order to prevent the appearance of mental health problems, also in the long term.

Many psychotherapeutic programs have been developed to combat stress. Interventions based on cognitive behavioral therapy (CBT) have proven effective for reducing stress, anxiety, and depression in different clinical populations [8–10]. Similarly, so-called “third wave” psychotherapies, such as mindfulness-based interventions (MBIs), compassion-based programs, and acceptance and commitment therapy (ACT), have also proved effective for reducing different psychopathological symptoms [11–15], including stress in healthcare professionals [16–21]. The most common format for the application of these psychotherapies has been face-to-face, both in group and individual therapy. However, for a few years, and particularly because of the pandemic, online psychotherapeutic programs have proliferated, making it possible to overcome obstacles to face-to-face attendance. They are very well suited to the needs of healthcare workers with schedules that are often difficult to reconcile [22].

There are a good number of online interventions (e.g., web-based, mobile applications, videoconference-delivered interventions, among others) aimed at treating stress, anxiety, depression, and insomnia, among others. Different studies have been published on the efficacy of online interventions to improve the quality of life and reduce the stress of healthcare workers. Some have verified that online CBT-based interventions are effective for reducing stress, suicidal ideation, or emotional distress in this population [20, 23–26], and others have also studied the efficacy of “third wave” online psychotherapies with positive results [27–30]. However, most of these programs have only achieved small effect sizes in terms of their effectiveness, and a fact that cannot be overlooked is that studies have also been published regarding online interventions found to be ineffective for reducing stress of healthcare workers, which makes further study into the characteristics of these programs and their possible limitations necessary. Moreover, the interventions that are tested in effectiveness studies are mostly discontinued once the study ends, which poses a major problem when it comes to the translation of efficacy studies on evidence-based interventions to daily clinical practice, a period estimated to be 17–20 years [31].

## Methods

### Study aims

This study aims to evaluate the effectiveness of a self-guided online program, MINDxYOU, based on “third wave” psychotherapy principles, for reducing the stress levels of healthcare workers through the practice of different exercises that promote mindfulness, acceptance, and self-compassion, in addition to indications on how to apply these skills to a healthy lifestyle. Furthermore, this project intends to emphasize the implementation of the intervention; implementation science is a discipline that is developing methods and procedures to ensure that evidence-based interventions are incorporated more quickly into daily clinical practice [32]. The implementation study includes 3 types of evaluation: 1) evaluation of the process (characteristics of the use of the intervention; measures before, during, and after implementation); 2) formative evaluation (adaptations for improvement based on participants’ feedback); and 3) summative evaluation (a compilation of the impact of the implementation strategy, evaluating the impact on indicators such as increase in the use of the intervention in the target context and economic impact).

As secondary aims, the impact of the intervention on other health-related outcomes such as psychopathological symptoms (depression, anxiety, and others) and process variables (resilience, mindfulness, compassion, and psychological flexibility) will also be evaluated, and an economic evaluation will be conducted.

### Study design

An effectiveness-implementation type 2 design will be used [33], since this study will assess both the effectiveness of the intervention and the implementation process in the same degree, as co-primary aims [34]. The empirical study will take a stepped wedge (SW) cluster randomized controlled trial design; this design implies that every participant starts the trial in the control phase (no exposure to the intervention), and then undertakes the intervention in a staggered and sequential way. Once it is completed (8 weeks), the maintenance phase takes place, during which the participant can continue to use the program at will, but without supervision. There will be three possible sequences (see Fig. 1), and each of the participating centers will be randomly assigned to one of them. The participants from each site will all follow the same sequence.

**Fig. 1 Fig1:**
[figure not shown]
The three possible sequences of the study phases. *Note:* A = Control phase; B = Intervention phase; C = Maintenance phase. Each cell represents a period of 8 weeks

SW designs are particularly recommended when the intervention being tested has strong evidence of positive effects or is very unlikely to cause harm [35], which is the case of our study. The present work is considered a closed cohort study, since all the study participants will start at the same time and will be evaluated at different time-points to be defined beforehand; the inclusion of new participants will not be allowed once the trial has commenced.

### Participants

The study sample will comprise healthcare workers currently working in clinical settings: a hospital, a primary care (PC) center, and a nursing home in the provinces of Zaragoza (Aragon) and Malaga (Andalusia), Spain. The following specific inclusion criteria will apply: 1) employment as a physician, nurse, physiotherapist, psychologist, nursing assistant, ambulance technician; a trainee student in any health profession; or employment in a nursing home assisting patients; 2) aged between 18 and 70; 3) ability to understand Spanish; 4) digital literacy and access to a smartphone, tablet, or personal computer with Internet connection; 5) prospects of continued employment at the same site for the following 6 months; and 6) provision of informed consent.

The following exclusion criteria will apply: 1) presenting with a disorder that affects the central nervous system; 2) diagnosis of a severe mental illness (including severe depressive disorders, suicidal tendencies, bipolar disorders, panic disorders, anxiety or stress-related disorders, obsessive–compulsive disorders, and substance-related disorders); 3) presenting with a medical, infectious, or degenerative illness that is not under control; and 4) expertise in “third wave” psychotherapies (i.e., meditation, mindfulness, etc.).

### Sample size

The sample size was calculated following the recommendations for SW designs [36]. First, the sample size for individual randomization needed to be determined; in this case, with an expected effect size of *d* = 0.50 for the primary outcome (Perceived Stress Scale, PSS) [37], which is a continuous variable, a statistical power of 80%, and an alpha level of 0.050, the required sample size would be 126 participants (N_1_). Subsequently, the following formula was considered:$$m=\frac{\mathrm{N}1 (1-p)}{\mathrm{K}-\mathrm{N}1\mathrm{p}}$$

where *m* is the necessary sample for each cluster and for each assessment moment (variable to be determined), N_1_ is the already calculated sample size (126), *p* is the intra-class correlation coefficient (assumed: 0.04), and *K* is the number of clusters (6). The result would be 24 participants per cluster, and assuming 20% attrition, 30 participants should be recruited from each site. This would imply a total sample of 180 participants.

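### The sample-size formula with its stated inputs gives 126 per cluster, not 24, and it is a parallel-cluster formula, so the basis given for 180 participants and 80% power does not hold as written

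*Protocol article*

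**What the plan says.** The Sample size section of the protocol article says that it follows recommendations for stepped-wedge designs. It starts from an individually randomised trial with an "expected effect size of *d* = 0.50 for the primary outcome", "a statistical power of 80%, and an alpha level of 0.050", and concludes that "the required sample size would be 126 participants" (N1).

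It then prints m = N1(1 − p)/(K − N1·p), where m "is the necessary sample for each cluster and for each assessment moment (variable to be determined"), p is the ICC, assumed to be 0.04, and K is the number of clusters, 6. It concludes: "The result would be 24 participants per cluster, and assuming 20% attrition, 30 participants should be recruited from each site". The total is given as 180.

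The Study design section describes a stepped-wedge cluster randomised trial with three sequences, in which whole centres are allocated to a sequence. It calls the study a closed cohort, and assessments are repeated every 8 weeks.

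**The concern.** The formula, all its inputs and its result are printed together, and they do not agree. The step that fails is the one that sets the size of the trial.

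The formula also looks wrong for the design. It contains nothing about the number of sequences or periods, or about the correlation between repeated measurements on the same person. In a closed-cohort stepped wedge these largely determine the precision of the treatment effect.

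At stake is the only justification given for 24 per cluster, 30 per site, 180 in total and 80% power on the primary outcome. As it stands, a reader cannot tell what effect on the Perceived Stress Scale (PSS) the trial can detect.

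**Working it through.** **Inputs from the Sample size section.** d = 0.50, power 80%, alpha 0.050, N1 = 126, p = 0.04, K = 6, stated m = 24, attrition 20%, total 180. Sidedness is not stated; two-sided is inferred because it reproduces N1.

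**1. Steps that reproduce.**
- N1: 2 × (1.96 + 0.84)² / 0.50² = 62.8, rounded up to 63 per arm, so 126.
- Attrition: 24 / (1 − 0.20) = 30 per site.
- Total: 6 × 30 = 180 recruited, or 6 × 24 = 144 evaluable.

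**2. The step that does not.**
m = 126 × (1 − 0.04) / (6 − 126 × 0.04) = 120.96 / (6 − 5.04) = 120.96 / 0.96 = **126 per cluster**.
That m equals N1 is a coincidence: 1 − p and K − N1·p are both 0.96.

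**3. What would give 24.**
- Keeping p = 0.04: K = 120.96/24 + 5.04 = 10.08.
- Keeping K = 6: p = (6 × 24 − 126) / (126 × 23) = 18/2898 = 0.0062.
- p = 0.005: 126 × 0.995 / (6 − 0.63) = 23.3, rounded up to 24.
- Changing N1 at p = 0.04 and K = 6 does not help: 128 gives 139.6, 100 gives 48, 64 gives 17.9 and 63 gives 17.4.

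**4. What the formula is.** Multiplying out gives K·m = N1[1 + (m − 1)p]. This is total sample size equals individually randomised size times the design effect of a parallel cluster trial measured once. Check: 126 × (1 + 125 × 0.04) = 126 × 6 = 756 = 6 × 126. It has no solution once p reaches 6/126 = 0.048, so 0.04 is already close to its limit.

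**5. What that formula implies for 24 per cluster.** Design effect 1 + 23 × 0.04 = 1.92; effective sample 144/1.92 = 75; power Φ(0.50 × √(75/4) − 1.96) = Φ(0.205) = 58%. This describes a parallel design, not this trial.

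**6. The actual type of design, under assumptions.** Figure 1 is not available and the article gives no autocorrelations, so these are assumed: a baseline assessment and then one every 8 weeks; crossovers at weeks 8, 16 and 24; 2 clusters per sequence; 24 evaluable per cluster; ICC 0.04; control versus intervention periods compared, with fixed period effects and maintenance periods left out. Total variance is set to 1. The covariance of the cluster-period means is ICC × [c on all pairs, 1 on the diagonal] + (1 − ICC)/24 × [r on all pairs, 1 on the diagonal], where c is the cluster autocorrelation (0.5–1) and r the individual autocorrelation (0–0.7). Generalised least squares gives the SE, and power is Φ(d/SE − 1.96).

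| c, r | SE (SD units) | d = 0.5 | d = 0.3 | d = 0.2 |
|---|---|---|---|---|
| 0.5, 0 | 0.175 | 82% | 40% | 21% |
| 0.8, 0 | 0.161 | 87% | 46% | 24% |
| 0.8, 0.5 | 0.127 | 98% | 66% | 35% |
| 1, 0.7 | 0.085 | >99% | 94% | 66% |

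A shorter four-period layout gives 85% to above 99% at d = 0.5, with c from 0.8 to 1 and r from 0 to 0.77.

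**7. Few clusters.** The normal approximation is generous with six clusters. As an illustration, take a t reference with 4 degrees of freedom (an assumption; critical value 2.776) and approximate power by P(t₄ > 2.776 − d/SE). At d = 0.5 this runs from about 53% (SE 0.175) through about 84% (SE 0.127) to about 98% (SE 0.085).

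**The case against.** The strongest defence is that the trial may well be large enough. A stepped wedge uses comparisons within clusters and within persons, so it can need far fewer participants than a parallel cluster trial with the same ICC. At d = 0.50 the planned 144 evaluable participants exceed 80% power throughout step 6. This stands. A reader might infer from 126 per cluster that the trial needs 756 evaluable participants (or 158 × 6 = 948 recruited), or that its power is really 58%. The article does not support either reading, because both figures come from a formula that does not fit the design.

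A second defence is a slip in reporting: an ICC of 0.005 would give 24 after rounding up. That is plausible but unconfirmed, since the text says 0.04. It would mend the arithmetic but not the choice of formula. Defining m per assessment moment does not mend it either, because no period or correlation term enters the formula.

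Third, a reader might take reference 37 as the source for d = 0.50 and call it a wrong citation. The reference follows the name of the PSS, as it does in the section on the primary outcome, so it cites the instrument. The Background does say that "most of these programs have only achieved small effect sizes in terms of their effectiveness", but the Discussion argues that tailoring to healthcare workers could increase the impact. So 0.50 may be optimistic, but it does not contradict the rest of the article. The source for it may be in the full protocol.

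**Conclusion.** The point holds. The printed formula and inputs give 126 per cluster, not 24, and the formula belongs to a one-measurement parallel cluster design. Both facts rest only on what the article prints, and no document outside it can make the formula, inputs and result agree. The justification for 24, 30, 180 and 80% power therefore fails as written.

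No shortfall in power is demonstrated, and adequacy is not demonstrated either. Over the assumed range the SE is about 0.085–0.175 SD. Power is at least about 82% at d = 0.5, 40–94% at 0.3 and 21–66% at 0.2. All are lower with small-cluster degrees of freedom, enough at the unfavourable end to fall below 80% even at d = 0.50. These ranges depend on the assumed layout, two clusters per sequence, the ICC of 0.04 and the autocorrelations. They show why the calculation must be redone and do not replace it.

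**What to change.** 1. Check the ICC and the number of clusters that were actually used, and correct whichever was misreported.
2. Replace the formula and the figure of 24 with a closed-cohort stepped-wedge calculation: three sequences, six clusters and their allocation to sequences, period effects, stated ICC, stated cluster and individual autocorrelations, and degrees of freedom suited to six clusters.
3. State the power, or the minimum detectable difference, that 180 recruited (144 evaluable) delivers at d = 0.50. Preferably add a smaller effect such as 0.2–0.3, given what the Background says about earlier programmes.
4. Confirm or revise 180 in the light of that result, rather than fixing it beforehand.

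The cost is one recalculation and one rewritten paragraph. Whether it also costs participants cannot be known until the calculation is done. The stated power may become less favourable, particularly at smaller effects.

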### Procedure

The strategy to recruit study participants will commence in October 2022. It will include indirect techniques such as informative posters in the selected hospitals/PC centers/nursing homes containing a brief explanation of the study and the website link; in addition, the occupational health service of the hospital and a member of staff at each site will contact their peers and send them an informative email with a brief explanation of the study and the website link. Consequently, any individuals interested in taking part in the study will find on the website all the details regarding the study procedures and aims, together with the rights of every participant and an explanation of the way in which their data will be processed.

Informed consent will then be documented via electronic signature, and complying candidates will undergo a basic screening process, which will consist of a checklist of the inclusion criteria. Candidates who meet these self-reported criteria will be presented with a schedule for the following 2 weeks and they will be asked to select a time for a 20-min video call or telephone call from a member of the research team who will conduct the complete screening of the participant, including the assessment of psychiatric diagnoses (MINI v7.0.2). Candidates who meet all the criteria will formally be included as participants in the study and will be offered information regarding the following procedures, which will start with a baseline evaluation including different self-reported questionnaires that the participant will complete using an online platform. The participant will receive via email or text message the link to the evaluation platform. Once the control phase is over, the participant will receive via email or text message their credentials (i.e., user and password) to access to the online intervention platform so they can start the MINDxYOU program. An external researcher, not related to this study, will conduct the randomization process to one of the three possible sequences using EPIDAT 4.2 (see Fig. 1).

Clear indications will be given on how to use the platform in the welcome module (see Table 1). Participants will be assessed for all the study variables every 8 weeks; the usability measure (System Usability Scale, SUS) [38] will be completed after finishing module 1 and module 4. The research team will record the usage that each participant makes of the platform: the number of times it was accessed, modules completed, and number of tasks delivered. Two external professionals, one in each province and unrelated to the research group, will be in charge of monitoring the intervention, providing feedback to the participants, and making weekly contact with participants via their preferred means (telephone call, text message, or email); this contact will be used to motivate participants to complete the intervention. Both professionals will previously have been trained in the contents and procedures of the MINDxYOU program by the research team. Once the intervention is complete, focus groups will be held in the provinces of Zaragoza and Malaga to qualitatively assess the acceptance and suitability of the intervention, and interviews will be conducted with managers and directors from each site to evaluate different aspects regarding implementation of the program.

**Table 1 Tab1:** Brief outline of the MINDxYOU program

Module	Main contents	Main practices
0. Welcome module	This module will introduce participants to the platform and present the main aims of the intervention	Participants will be given the opportunity to share their feelings and needs, and will receive feedback from the research team
1. Mindfulness	The concept of mindfulness will be explained, together with its applications for stress reduction and the promotion of good mental health	Body scan, sitting meditation, three-minute breathing meditation
2. Compassion	The concept of compassion will be explained, together with its applications for stress reduction and the promotion of good mental health	Compassionate breath meditation, compassionate body scan, safe place meditation
3. Acceptance	The concept of acceptance will be explained, together with its applications for stress reduction and the promotion of good mental health	Meditation focused on acceptance, identification of personal values
4. Healthy lifestyle	Instructions on how to apply the concepts of mindfulness, compassion, and acceptance to the main aspects of a healthy lifestyle: physical activity, diet, sleep, and socialization	Mindfulness and compassion exercises applied to physical activity, diet, sleep, and socialization

